### Adherence to protocol and losses to follow-up

Previous studies by our group reveal high study adherence rates, with > 90% wearing their full dentures over the course of 6 months [41, 57–59]. This RCT provides variations of a treatment sought by participants at university clinics, with no major change in their routine. Subsequent follow-ups following the end of this RCT will also elucidate adherence rates for longer periods. As much as possible, we set up the intervention schedule, follow-up, and data collection to resemble traditional oral healthcare procedures. We will also have the RA communicate with the participants using their preferred communication method (e.g., phone, text, e-mail) to verify possible adverse events, such as pain under the denture base, that may require a rapid adjustment visit. Those events and consequent conducts will be reported as part of the outcome variable “5. Adverse effects”.

### Analytical plan

#### Quantitative analysis

We will enter and analyze outcome data in a blind fashion at the end of data collection. The TC will enter data in spreadsheets by randomly coding the interventions as 1 and 2, and the data analyst will be unaware of their meaning until the end of statistical testing. Data will undergo descriptive analysis, with substantial deviations from normality leading to variable transformation. Generalized estimating equations (GEE) will be used to test the effect of interventions, follow-up time, and gender as independent variables, with 95% confidence intervals. Other approaches to assess the primary outcome will involve the inclusion of age, baseline results, and previous denture wearing in separate models, one covariate at a time.

A limitation with regard to GEE is that compared to parametric normal theory methods that necessitate the missing data to be missing at random, GEE methods impose a more stringent condition, requiring the data to be missing completely at random. Our results will be evaluated according to the intention-to-treat principle. In the case of unbalanced missing data among interventions or loss of 5% (*n* > 2) or more of participants, different strategies will be attempted for imputing primary outcome data, as recommended by Dziura et al. [60]; multiple imputation will be used for patient satisfaction based on least squares regression with at least five datasets. In the case of “missing not at random” (MNAR) data, analyses will be repeated after a baseline-observation-carried-forward approach (i.e., withdrawn participants will be considered as dissatisfied as prior to receiving dentures). A second analysis will be performed with imputed values and cross-checked.

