### Sample size estimation

The planned enrollment comprises 26 participants, based on overall patient satisfaction. A minimal important difference of 10 mm (10% of the VAS) was used for the estimation, as done in previous RCTs [41, 54]. A standard deviation of 7.5 mm was chosen for the difference in satisfaction [55]. Considering a 2-sided alpha of 0.01 to compensate for the number of secondary outcomes and a power of 90%, the RCT requires *n* = 21 for superiority hypothesis testing (i.e., the confidence interval for between-treatment differences would exclude zero) [56]. The final sample size is drawn from including further 20% to the planned *n* to compensate for possible dropouts; although withdrawals will unlikely pass 10% [41, 55, 57], additional participants may be lost due to aging-related issues (e.g., worsening of systemic diseases, and death).

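### The sample size is set at two-sided alpha 0.01 with a confidence-interval criterion for superiority, but the analysis section gives only 95% intervals and no 0.01 threshold

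*Protocol article*

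**What the plan says.** Under Sample size estimation, the protocol article sizes the trial on overall satisfaction: "Considering a 2-sided alpha of 0.01 to compensate for the number of secondary outcomes and a power of 90" per cent. The target is stated as "A minimal important difference of 10 mm (10% of the VAS) was used for the estimation", and for the spread, "A standard deviation of 7.5 mm was chosen for the difference in satisfaction". The result is that "the RCT requires *n* = 21 for superiority hypothesis testing", which the same sentence explains in interval terms: "the confidence interval for between-treatment differences would exclude zero". No confidence level is attached to that interval, but the sentence that contains it sets alpha at 0.01.

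Under Analytical plan, Quantitative analysis, the only inferential statement with a level is this: "Generalized estimating equations (GEE) will be used to test the effect of interventions, follow-up time, and gender as independent variables, with 95% confidence intervals". That section contains no 0.01 threshold, no 99% interval and no other rule for multiple outcomes.

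**The concern.** An alpha used to choose n protects nothing by itself. Error control comes from the threshold applied to the results. The sample size section implies a 99% interval, since alpha is 0.01 and superiority means that the interval excludes zero. The analysis section names a 95% interval, and a 95% interval that excludes zero is a two-sided 0.05 test. A result with p between 0.01 and 0.05 can therefore be called superior by one section and not by the other.

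The point is not that a multiplicity procedure is absent, which could be left to an analysis plan that is not shown. The article states an alpha, its purpose and an interval criterion, and then gives an interval level that does not match them. If this is settled only after the results are seen, the choice of rule could depend on them. The stricter alpha was introduced to allow for the secondary outcomes, so they are most affected.

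**Working it through.** **Inputs from Sample size estimation.** Difference 10 mm; SD 7.5 mm, described as the SD of the difference; two-sided alpha 0.01; power 90%; n = 21 before dropout; 26 enrolled. **From Quantitative analysis:** 95% intervals.

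**Step 1: the plan's own figure.** I used a paired t-test with the noncentral t distribution, alpha 0.01 and power 0.90.
- SD of the difference 7.5 mm, as worded: n = 12.
- 7.5 mm assumed to be the within-participant SD, so SD of the difference = 7.5 × √2 = 10.61 mm: n = 21, the stated figure.
- Dropout: 21 × 1.2 = 25.2, rounded up to 26.

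The stated n is thus reproduced at alpha 0.01 under the second reading. Which reading was meant is a separate question. Both are carried forward because the mismatch in level exists under either. The 10.61 mm is my assumption and does not appear in the article.

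**Step 2: the smallest observed difference whose interval excludes zero.** Half-width = t(1 − α/2, n − 1) × SD / √n. At n = 21 the quantiles on 20 df are 2.086 (95%) and 2.845 (99%).

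| SD of difference | SD/√21 | 95% half-width | 99% half-width |
|---|---|---|---|
| 7.5 mm | 1.637 | 3.41 mm | 4.66 mm |
| 10.61 mm (assumed) | 2.315 | 4.83 mm | 6.59 mm |

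Observed differences between the last two columns are positive at 95% but not at the planned alpha. If all 26 complete, the bands are 3.03 to 4.10 mm and 4.28 to 5.80 mm.

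**Step 3: width of the intervals.** The 99% to 95% ratio is 2.845/2.086 = 1.36 with t on 20 df. With normal quantiles, as is usual for GEE, it is 2.576/1.960 = 1.31. So 99% intervals are 31 to 36% wider.

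**Step 4: multiple outcomes, as an illustration.** The chance of at least one false positive in k independent tests is 1 − (1 − α)^k. Counting six specific satisfaction aspects, the OHIP-EDENT total and four domains, and FAD gives k = 12. That count is mine; the article does not list 12 tests.

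| k | at 0.05 | at 0.01 |
|---|---|---|
| 5 | 22.6% | 4.9% |
| 7 | 30.2% | 6.8% |
| 12 | 46.0% | 11.4% |

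**Step 5: power at alpha 0.01 for 10 mm.** With SD 10.61 mm, power is 91.6% at n = 21 and 97.1% at n = 26. With SD 7.5 mm it exceeds 99.8% at both. At alpha 0.05, 90% power would need only n = 14 (SD 10.61 mm) or n = 9 (SD 7.5 mm).

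**The case against.** The two sections can be reconciled. The analysis section states no significance threshold and no success rule. The only criterion for superiority is in the sample size paragraph, beside alpha 0.01. On that reading, tests are made at 0.01 and the 95% intervals are for estimation. This stands as a possible reading, so it cannot be said as fact that error control is lost. But the article does not say it, and the analysis section attaches the 95% level to the verb for testing.

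Four stronger readings that a reader might infer are not supported:
- *That the primary comparison is left unprotected.* One primary outcome is named, and a 95% interval holds that single test at the conventional 5%. This is five times the planned 1% only if the 95% interval is the decision rule.
- *That the article promises 0.01 for each secondary outcome.* It gives the number of secondary outcomes as the reason for the stricter alpha in sizing the trial. Testing each at 0.01 is a plausible inference, not a stated commitment.
- *That 46% is the real false-positive risk.* It assumes independence. Satisfaction aspects from one questionnaire, and a total score with its own domains, will be correlated.
- *That 0.01 would have given full family-wise control.* The 11% for 12 independent tests shows that it is only a partial allowance.

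The practical effect on the primary result may also be small. The disputed bands lie wholly below the 10 mm minimal important difference. If the true difference is 10 mm and n = 21, the two thresholds disagree with probability of about 0.1% (SD 7.5 mm; 0.9999 − 0.9986) or 7% (SD 10.61 mm; 0.984 − 0.916). The disagreement matters mainly for small differences and for the secondary outcomes.

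**Conclusion.** The inconsistency is real and lies in the current text: alpha 0.01 with an interval criterion in one section, and 95% intervals as the only stated level in the other. If the 95% interval is the decision rule, the test runs at 0.05 and the planned allowance for multiple outcomes is not applied. At n = 21 the two rules then disagree for observed differences of about 3.4 to 4.7 mm on the SD as worded, or about 4.8 to 6.6 mm on the assumed within-participant reading. These bands come from a paired-t approximation to the planned GEE. That the analysis will in fact be read at 0.05 is not established; the document leaves it open, and it should not.

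**What to change.** Before the treatment codes are broken, add to Quantitative analysis that superiority on overall satisfaction is judged at two-sided 0.01, equivalently that the 99% confidence interval for the treatment difference excludes zero. Apply the same 0.01 threshold to the secondary outcomes and say that it is a partial allowance for their number. 95% intervals may still be reported if they are labelled as estimation only. Naming another multiplicity rule would also resolve the conflict, but 0.01 is the level for which the trial was sized.

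The cost is a stricter threshold, with decision intervals about 31 to 36% wider than 95% intervals. No extra participants are needed, and the stated power is not reduced because it was calculated at 0.01.

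### Primary GEE test with 21 to 26 participants needs a small-sample correction: the ordinary version rejects about 7–8% of the time at nominal 5% and 2.1–2.5% at nominal 1%

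*Protocol article*

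**What the plan says.** Protocol article, Quantitative analysis: "Generalized estimating equations (GEE) will be used to test the effect of interventions, follow-up time, and gender as independent variables". The intervals attached to this are at 95%. The section states no variance estimator, reference distribution, working correlation or small-sample correction.

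The same section contrasts GEE with normal-theory methods, which it says need only data missing at random, and concedes that "GEE methods impose a more stringent condition, requiring the data to be missing completely at random". It then provides multiple imputation of patient satisfaction if missing data are unbalanced between interventions or losses reach 5%, and a repeat with the baseline observation carried forward if data are missing not at random.

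Before modelling, the data are to be described, "with substantial deviations from normality leading to variable transformation".

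Sample size estimation: "The planned enrollment comprises 26 participants, based on overall patient satisfaction", of whom 21 are required evaluable. "A minimal important difference of 10 mm (10% of the VAS) was used for the estimation", and "Considering a 2-sided alpha of 0.01 to compensate for the number of secondary outcomes and a power of 90"% was set.

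**The concern.** Ordinary GEE inference relies on a large number of independent clusters. Here the cluster is the participant, so there are 21 to 26. At that size the uncorrected sandwich variance is biased downward, and a normal reference ignores the uncertainty in the variance estimate. Both errors go the same way: intervals are too narrow and false positives too frequent, in relative terms most of all at the 0.01 level used for sizing.

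Two lesser points concern the same choice of method. First, the plan names the stricter missing-data condition of GEE and an alternative without it, and gives no reason for preferring GEE for a VAS score measured once after each of two periods. Second, the transformation rule could move the primary estimate off the mm scale on which the important difference is defined. GEE does not need normal outcomes, and in a cross-over the distribution that matters is that of the within-person difference, not of the raw score.

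**Working it through.** **Inputs from the article.** n = 21 evaluable and 26 enrolled; two periods with one primary assessment each; 1:1 sequence allocation; two-sided alpha 0.01 in the sizing and 95% intervals in the analysis, so both levels are checked. **Assumptions, not in the article:** uncorrected sandwich with normal reference, normal outcomes, no carry-over, within-person correlation 0.5 (0.8 also tried at n = 21).

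**The plan's own figure.** With a difference of 10 mm, two-sided alpha 0.01 and 90% power, a noncentral-t calculation for a cross-over gives n = 21 if 7.5 mm is the within-subject SD (SD of the difference 7.5 × √2 = 10.6). If 7.5 mm is the SD of the difference, as the section words it, 12 or 13 suffice (n−1 or n−2 degrees of freedom). Either way 21 is enough for the t-based analysis. Adding 20% gives 21 × 1.2 = 25.2, rounded up to 26.

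**Closed form, complete data, equal sequences** (approximate at n = 21, where the split is 11 and 10).

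- The GEE treatment estimate is the period-adjusted within-person difference; sex is constant within a person and drops out of it.
- The sandwich divides the residual sum of squares of the within-person differences by n; the t-test divides it by n−2. So SE(sandwich) = SE(t-test) × √((n−2)/n).
- n = 21: √(19/21) = 0.951. n = 26: √(24/26) = 0.961.
- An SE estimated on few degrees of freedom is also slightly low on average, by a factor of about 1 − 1/(4(n−2)): 0.987 and 0.990. The products are 0.951 × 0.987 = 0.939 and 0.961 × 0.990 = 0.951. Simulated mean SE ratios are 0.936–0.940 and 0.948. The SE is therefore about 6% too small at n = 21 and 5% at n = 26.
- Actual rejection rate = 2 × P(t with n−2 df > z × √((n−2)/n)).
  - n = 21: 5% level, 1.960 × 0.951 = 1.864, giving 0.078; 1% level, 2.576 × 0.951 = 2.450, giving 0.024.
  - n = 26: 5% level, 1.960 × 0.961 = 1.883, giving 0.072; 1% level, 2.576 × 0.961 = 2.475, giving 0.021.

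**Simulation under no treatment effect** (8,000 to 30,000 trials per setting, including a check in standard GEE software):

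| Method | n | Nominal 5% | Nominal 1% |
|---|---|---|---|
| Uncorrected sandwich, normal reference | 21 | 7.6–8.2% | 2.2–2.5% |
| Uncorrected sandwich, normal reference | 26 | 6.9–7.3% | 2.1–2.3% |
| Uncorrected sandwich, t(n−2) | 21 and 26 | 5.8–6.3% | 1.2–1.4% |
| Mancl-DeRouen, t(n−2) | 21 and 26 | 4.0–4.2% | 0.7–0.8% |
| Period-adjusted cross-over t-test | 21 and 26 | 4.8–5.2% | 0.9–1.2% |

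The ratios for the uncorrected version are about 1.4–1.6 at 5% and 2.1–2.5 at 1%. Coverage of a nominal 95% interval is 1 minus the rejection rate, about 92–93%.

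**Does missing data cause it?** With n = 26, no imputation and 20% of participants missing period 2 completely at random, the rate at nominal 1% is 2.0–2.2%. With 10% or 20% lost depending on the period-1 score, it is 1.7–2.0%. Bias in the treatment effect is about zero (at most 0.002 SD). The inflation is present with complete data, and these losses do not raise it. Dropout that differs by treatment could bias the estimate, but the article gives no rate for it and it was not simulated.

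**The case against.** The strongest objection is that the inflation belongs to an estimator that the article never names. A corrected variance with a t reference may stand in the full protocol or an SAP that is not shown, and a condensed article may leave that detail out. This stands in part: the error rates are conditional, and the silence alone would not be a finding. What remains is that the article commits the primary test to a method whose ordinary form does not hold its level at the stated sample size, while an equally simple method does.

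A reader might also infer that the plan admits its standard errors are too small, or that the missing-completely-at-random condition produces the excess rejections. The article supports neither. Its concession covers the missing-data condition only, and the excess appears without any missing data.

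Nor would it be fair to say that the plan sees the limitation and does nothing. Multiple imputation before GEE is an accepted way to relax the condition to missing at random, and a repeat analysis for data missing not at random is added. The gap is narrow: below the trigger, with small and balanced losses, GEE is used without imputation.

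On transformation, the rule is conditional and applies to the outcome data generally. The sizing section frames success as an interval that excludes zero, and no stated rule compares the estimate with 10 mm. A transformation would therefore not invalidate the test. It would leave an estimate that cannot be read directly against the difference used for sizing.

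**Conclusion.** The concern holds in conditional form. If the primary GEE is run with an uncorrected sandwich variance and a normal reference, standard errors are about 5–6% too small at 21 to 26 participants. The test rejects about 7–8% of the time at nominal 5% and 2.1–2.5% at nominal 1%, and a 95% interval covers about 92–93%. The closed form and the simulations agree. The figures rest on normal outcomes and no carry-over; changing the within-person correlation from 0.5 to 0.8 at n = 21 hardly moved them.

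The unconditional statement, that this trial's primary test will reject at twice its level, is not supported: the estimator is not stated, and the multiple is just over two only at 1%. The missing-data condition is a separate and smaller weakness, partly met by the planned imputation. The transformation rule is a secondary matter of interpretation.

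**What to change.** State one of these as the primary analysis:

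- GEE with a small-sample-corrected sandwich variance (for example Mancl-DeRouen) and a t reference; or
- a linear mixed model with a random participant effect, fixed effects for treatment, period and sex, and Kenward-Roger degrees of freedom. With complete data this is essentially the period-adjusted cross-over t-test. It also needs only missing at random throughout, so it does not depend on the imputation trigger.

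Report the primary treatment difference on the untransformed mm scale, and use a permutation or bootstrap analysis of the within-person differences as the check for non-normality.

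The cost is a few sentences, standard software and slightly wider intervals. No larger sample is needed: at n = 21 and alpha 0.01 the cross-over t-test has 91% power if 7.5 mm is the within-subject SD and 99.9% if it is the SD of the difference.

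### The imputation trigger's percentage and count disagree for 26 participants, and baseline-observation-carried-forward does not suit a cross-over comparison of two new denture pairs

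*Protocol article*

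**What the plan says.** All of this is in the protocol article. Under Analytical plan, Quantitative analysis, imputation of the primary outcome is called for when missing data are unbalanced between interventions, or on "loss of 5% (*n* > 2) or more of participants". Multiple imputation by least squares regression, with at least five datasets, is the named method for patient satisfaction. For data missing not at random (MNAR), "analyses will be repeated after a baseline-observation-carried-forward approach (i.e., withdrawn participants will be considered as dissatisfied as prior to receiving dentures").

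Under Sample size estimation: "The planned enrollment comprises 26 participants, based on overall patient satisfaction". The target difference is fixed there too: "A minimal important difference of 10 mm (10% of the VAS) was used for the estimation". The same section judges withdrawals above 10% unlikely and then adds that "additional participants may be lost due to aging-related issues (e.g., worsening of systemic diseases, and death").

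Under Outcome assessment timeline, the satisfaction questionnaire (MDSQ) is completed at baseline, before either trial pair is delivered, and again after 3 months with each pair.

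**The concern.** The trigger states one threshold in two ways, as a percentage and as a count. If they differ at a plausible number of losses, the plan does not say whether to impute in that case.

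BOCF raises a separate problem. In a parallel-group trial it is a crude penalty that can fall on either arm. In this cross-over the treatment effect is a within-person contrast between two new denture pairs, and the baseline score belongs to neither. Someone who leaves after the first assessment keeps a real score for the first pair and receives the old denture's score for the second. That contrast measures new against old, not 3D-printed against conventional. At stake is whether the MNAR analysis can serve as a robustness check, since in a trial of 26 a few such values can move it for reasons unrelated to fabrication method.

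**Working it through.** **1. Trigger.** Input: 26 participants (Sample size estimation).

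- 5% of 26 = 0.05 × 26 = 1.3, so a loss of 5% or more means at least 2 people.
- A count above 2 means at least 3 people.
- Two losses: 2/26 = 7.7%, percentage met, count not met.
- Three losses: 3/26 = 11.5%, both met.

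Using the evaluable 21 does not help (0.05 × 21 = 1.05). A base of 52 person-periods would fit (0.05 × 52 = 2.6), but the text refers to participants. Two losses are within the plan's own expectation, since 10% of 26 is 2.6.

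**2. BOCF shift.** Let A and B be the two pairs, with 13 participants per sequence. Let k_AB and k_BA be the numbers lost after the first assessment in each sequence, and let the gain be the mean score on a new pair minus the mean score on the old denture. With no true difference, the A minus B contrast of a lost participant is +gain in sequence AB and −gain in sequence BA. Averaging the two sequence means gives

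shift = (k_AB − k_BA)/26 × gain.

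The documents do not state the gain. I assume 10 to 35 mm.

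| Losses (AB:BA) | Gain 10 mm | Gain 20 mm | Gain 35 mm |
|---|---|---|---|
| 1:1 | 0 | 0 | 0 |
| 2:1 | 10/26 = 0.4 mm | 20/26 = 0.8 mm | 35/26 = 1.3 mm |
| 3:0 | 30/26 = 1.2 mm | 60/26 = 2.3 mm | 105/26 = 4.0 mm |

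These compare with a minimal important difference of 10 mm.

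**3. Dilution under balance.** Suppose A is truly 10 mm better and one person is lost per sequence. The AB loss contributes gain + 10 and the BA loss −gain. Together they add 10 where two complete participants would add 20. The estimate is (260 − 10)/26 = 9.6 mm.

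**4. Effect on the test.** Simulation with 13 per sequence, the plan's SD of the difference of 7.5 mm, an assumed SD of 15 mm for the individual gain, and a period-adjusted comparison standing in for the GEE.

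| Losses | No true difference: rejection at nominal 5%, gain 10 / 20 / 30 mm |
|---|---|
| 3:0 | 7% / 12% / 16% |
| 2:1 | 4% / 2.5% / 1.3% |
| 1:1 | 4% / 2.5% / 1.0% |

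If three losses fall at random, all lie in one sequence with probability 2 × C(13,3)/C(26,3) = 572/2600 = 0.22. Weighting at 20 mm gives 0.22 × 11.7% + 0.78 × 2.5% = 4.5%, so there is no inflation on average.

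With a true 10 mm difference and a 1:1 loss, power at the two-sided 0.01 used for sizing is 98.6%, 96.0% and 89.6% for gains of 10, 20 and 30 mm, against practically 100% without losses.

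**The case against.** The strongest reply is that BOCF is not the primary analysis. Multiple imputation comes first, and BOCF is a deliberately pessimistic repeat for the MNAR case. If people leave because the second pair is poor, penalising that pair is its purpose. This stands as to severity. It does not rescue the method, because the size of the penalty is set by how bad the old denture was, not by any stated assumption about the missing score.

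A reader might infer four stronger things that the documents do not support.

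- **That BOCF generally creates a false treatment difference.** The net shift needs losses unbalanced between sequences. Someone lost before the first assessment gets baseline for both pairs and contributes a zero difference.
- **That false positives rise to about 16 to 18%.** That needs a gain of around 30 to 35 mm, which no document gives, and all three losses in one sequence. Near-balanced splits make the test conservative.
- **That BOCF contradicts the reasons for loss the plan expects.** Sample size estimation lists illness and death in addition to ordinary withdrawals, and the BOCF clause concerns withdrawn participants.
- **That the trigger lets the team steer the result.** The conflict matters only at exactly two losses. If both leave the same pair unscored, the separate imbalance criterion applies anyway. The analyst is also blind to the treatment codes until testing ends.

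Making BOCF conditional on MNAR can fairly be read as an assumption rather than a claim to detect it. Even so, observed data cannot show when the condition is met, so the analysis is better run unconditionally.

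**Conclusion.** Both faults stand, with limited consequences. The trigger inconsistency is plain arithmetic and needs no assumption: at two losses the plan gives two answers. The BOCF fault follows from the design: baseline scores neither treatment, so a participant lost after the first assessment no longer informs the comparison of interest. The effect on the sensitivity estimate runs from nil, when losses balance between sequences, to about 1.2 to 4.0 mm when three losses fall in one sequence. Those figures rest on the assumed gain of 10 to 35 mm and the rejection rates also on the assumed SD of 15 mm. The plan's own imbalance criterion calls for imputation in cases where missing scores are unequal between interventions, and unequal losses between sequences are where the shift does not cancel. Severity is minor to moderate.

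**What to change.** 1. Make the two thresholds agree, for example 5% or more of participants, i.e. n ≥ 2. Alternatively, drop the trigger and run the missing-data analyses whenever a primary score is missing.
2. Replace BOCF with a prespecified sensitivity analysis that does not wait for the data to be declared MNAR. Impute the missing period score by multiple imputation, using the participant's observed score from the other period together with treatment and period. Then shift the imputed scores by a stated range of deltas, one treatment at a time, and report the delta at which the conclusion changes (tipping point).

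The cost is a few lines of analysis wording and a little programming. Sample size, visits and data collection are unchanged.
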